### Statistical Analyses

The analysis employs an intent-to-treat analysis design. The percentage of HIV-positive individuals who achieve viral suppression and report being fully engaged in care will be compared across arms, using Chi-square tests for significant difference. Retention in care is measured as the number of 6-month blocks during which at least one clinic visit was attended over the 2-year period following an initial attended visit; the percentage of HIV-positive individuals who report full retention in care (one clinic visit during each 6-month block) and the number of 6-month blocks during which care was received will be compared across study arms, using the appropriate tests for statistical significance. The capability of the intervention to yield longer-lasting effects in adherence endpoints over time will be examined. The visual analog scale data over the course of the study, at baseline and follow-up, will be analyzed using generalized linear models (GLMs) with properly-chosen (based on the distribution of dependent variables) link functions to analyze longitudinal adherence outcome data. The GLMs will be estimated using generalized estimating equations (GEE) with robust standard error estimates, which provide an extension of regression analyses to the cases of correlated or repeated observations and allows for inclusion of both categorical and count-dependent variables, and for appropriate modeling of covariance structures when observations are correlated across time. With appropriate link functions, GLMs can readily handle dependent variables with normal distributions, dichotomous outcomes, count data (Poisson distribution), and over-dispersed or zero-inflated count data (negative binomial models). The models will include the dyadic characteristics scales to examine the extent to which adherence is shaped by relationship functioning.

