### Incidence of Aggregate “Sex at Risk” Within Partnerships

At-risk sex will be defined as any CAI that occurs within the partnership during the follow-up period, even if the HIV-negative partner is taking PrEP or the HIV-positive partner has achieved viral suppression, in accordance with current CDC recommendations on PrEP and condom use [65]. The incidence of at-risk sex acts will be calculated as an incidence density, with the numerator being number of individual at-risk sex acts, and the denominator being person-years of follow time. Comparisons of the incidence of at-risk sex acts will be made by comparing incidence densities between the two arms. Incidence rates per couple-year of follow-up will be estimated and compared using exact methods based on the Poisson distribution when there are fewer than 15 events per subgroup or, when there are at least 15 events per group, by using the GEE approach. Baseline covariates include race, age, and duration of relationship. Period incidence rates (6-monthly incidence density rates) of at-risk sex will be estimated by performing a GEE Poisson regression analysis of the 6-monthly counts, implemented using the SAS PROC GENMOD procedure [66], and using an exchangeable correlation structure for the repeated observations of couples. The incidence density ratio (or incidence rate ratio; IRR) is the ratio of the incidence density in one treatment group (intervention arm) to that of a control group (standard of care). Results by each baseline covariate will be summarized as the IRR and the 95% confidence interval. In addition, we will tabulate data on disclosure of sex outside the relationship, the percentage of couples with agreements about sex outside the relationship, and the percentage of couples reporting agreement breakage or change in agreements. Prevalence of each outcome will be calculated, and prevalence of outcomes will be compared in the control and intervention groups using Chi-square tests or Fischer’s exact tests, as appropriate.

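### The switch to GEE counts sex acts rather than couples, so incidence rate ratios in small subgroups could have intervals that are too narrow (minor; secondary outcome)

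*Protocol article*

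**What the plan says.** All of this is in the protocol article's section on the incidence of aggregate sex at risk within partnerships, unless noted.

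- The incidence density counts acts, with "the numerator being number of individual at-risk sex acts".
- The lower branch of the rule is "exact methods based on the Poisson distribution when there are fewer than 15 events per subgroup". The upper branch applies "when there are at least 15 events per group, by using the GEE approach".
- Period rates come from "performing a GEE Poisson regression analysis of the 6-monthly counts, implemented using the SAS PROC GENMOD procedure", "using an exchangeable correlation structure for the repeated observations of couples". The couple is therefore the cluster.
- On covariates: "Baseline covariates include race, age, and duration of relationship". On reporting: "Results by each baseline covariate will be summarized as the IRR and the 95% confidence interval".
- Robust errors are named only under Statistical Analyses, for the adherence models, which are "estimated using generalized estimating equations (GEE) with robust standard error estimates".

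The rule has no condition on the number of couples. The article gives no act rate, covariate categories or stratum sizes.

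**The concern.** The GEE sandwich variance is a large-sample result in the number of independent clusters. With few couples it is biased downwards, and a normal reference makes the intervals narrower still, however many acts those couples report. A threshold in acts does not guard against this. A couple with 5 acts per 6 months has 5 × 4 = 20 acts over 24 months, so one couple alone can pass 15.

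At stake are the confidence intervals for rate ratios in small strata of race, age or relationship duration. If they are too narrow, chance differences between a handful of couples can look like subgroup effects.

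**Working it through.** **Inputs from the article.** Sample Size: 165 couples and 80% retention, so 165 × 0.80 = 132, or about 66 per arm with roughly equal allocation. Design: visits at 6, 12, 18 and 24 months, so four 6-month counts per couple. The figure of 15 has no stated derivation and cannot be reproduced.

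**Assumed, because the article gives no figure.** Mean acts per couple per 6 months of 1, 5 or 15. Gamma variation between couples with variance 0.5, 1 or 2, and for variances 1 and 2 also with 40% of couples having no acts. Two-sided 5% tests and uncorrected robust errors.

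**Stratum size.** A category holding 10% of couples has 0.10 × 66 ≈ 7 per arm. Four to 10 per arm corresponds to 4/66 = 6% to 10/66 = 15% of couples.

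**Does the rule let such strata through?** At a mean of 5 acts, both arms reached 15 acts in 49% to 98% of simulated trials with 3 couples per arm, and in 85% to 100% with 6.

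**Test statistic.** With k couples in an arm, couple totals yᵢ and mean ȳ, the arm-only exchangeable Poisson GEE in balanced data has robust variance

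V = Σ(yᵢ − ȳ)² / (k²ȳ²),

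and z = log(ȳ₁/ȳ₀) / √(V₁ + V₀), rejecting if |z| > 1.96.

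**Rough analytic check.** V uses divisor k where k − 1 is needed. If couple totals were near normal, the true error would be about P(|t with 2k − 2 df| > 1.96 × √((k − 1)/k)):

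- k = 4: cut-off 1.70 on 6 df, about 14%
- k = 10: cut-off 1.86 on 18 df, about 8%
- k = 66: cut-off 1.95 on 130 df, about 5.4%

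The number of acts does not enter. Skewed act counts make the small-k figures worse.

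**Simulation under no effect** (20,000 runs per setting, keeping only runs with at least 15 acts in each arm). False-positive rate, range over the variation settings:

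| Couples per arm | Mean 5 or 15 acts | Mean 1 act |
|---|---|---|
| 4 | 11.6% to 22.0% | 1.1% to 5.5% (3 to 6 per arm) |
| 6 | 11.8% to 19.5% | as above |
| 10 | 9.1% to 15.7% | 5.1% to 8.8% |
| 20 | 7.2% to 10.5% | 6.9% to 9.5% |
| 66 | 5.4% to 6.9% | 5.7% to 6.7% |

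At 3 to 10 couples per arm and mean 5 or 15, the median robust standard error was 0.61 to 0.92 of the true standard deviation. A separate simulation at 5 or 15 acts gave 16% to 23% at 4 per arm, 12% to 17% at 6 and 9% to 13% at 10. Fitting an actual GEE (arm plus period, mean 5, variance 1) gave 19.5%, 14.8%, 11.2% and 8.4% at 4, 6, 10 and 20 per arm.

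At 1 act per 6 months, 4 couples expect only 4 × 4 = 16 acts. Keeping only trials with at least 15 in both arms holds the two totals close together, so there is no inflation. At 10 per arm the maximum is 8.8/5 ≈ 1.8 times nominal.

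**The other branch.** At 6 to 10 couples per arm and very low act rates, the exact Poisson test rejected 9.6% to 12.7% (variance 1) or 16.0% to 21.0% (variance 2), because it treats acts within a couple as independent.

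**The case against.** A reader might infer that subgroup rate ratios under this plan generally carry two to four times the nominal error. The document does not support that. It gives no act rate, between-couple variation, categories or stratum sizes. The inflation is confined to roughly 4 to 10 couples per arm with frequent acts. A median split of age or relationship duration would leave about 33 per arm, and the simulated rate at 30 per arm with mean 5 or 15 was only 6.5% to 8.7%.

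Three further objections carry weight:

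- The at-risk sex section names GEE and the procedure, but neither robust errors nor the absence of a small-sample correction. An analysis plan that is not shown may settle this.
- Reporting by each baseline covariate may mean covariate terms in one full-cohort model. The word subgroup in the rule favours strata, but the same sentence then says group.
- The figure 15 is not the sole cause. Exact Poisson is no refuge for few-couple strata, and GEE at least respects the couple as the cluster.

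None of this rescues the rule itself. The article states it, and it counts the wrong unit.

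**Conclusion.** The criticism of the rule holds; its size is conditional. The choice of method rests on acts, while the validity of the GEE branch rests on couples. If ratios are reported within strata with uncorrected robust errors, the false-positive rate is roughly 9% to 23% at about 4 to 10 couples per arm with about 5 or more acts per 6 months, and about 7% to 10% at 20 per arm. At about 1 act per 6 months the inflation is absent at 4 to 6 per arm and at most about 1.8-fold at 10. The full-arm comparison stays near 6%.

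Sexual risk-taking is a secondary outcome under Outcomes, and no primary conclusion depends on this. It is a minor point, worth correcting because the correction is cheap.

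**What to change.** 1. Choose the method by the number of couples per arm in the group, fixed before unblinding. Any particular cut-off is a judgement and should be justified, for instance from pooled act rates.
2. For subgroup ratios, use a small-sample corrected sandwich variance with a t reference, such as Mancl-DeRouen. In simulations at 5 or more acts this gave about 3% to 8% at 4 to 10 couples per arm.
3. For very few couples, use a couple-level permutation test or show rates without a test. With 3 per arm there are only 20 allocations, so the smallest two-sided p-value is 2/20 = 0.10; with 4 per arm it is 2/70 = 0.03. Do not fall back on exact Poisson.
4. State whether results by covariate means strata or model terms.

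The cost is one reworded rule and wider subgroup intervals, with no new data. In the balanced arm-only case Mancl-DeRouen multiplies the standard error by k/(k − 1). With the t reference, the interval on the log scale widens by (4/3) × (2.447/1.96) ≈ 1.66 at 4 couples per arm, (10/9) × (2.101/1.96) ≈ 1.19 at 10, and (66/65) × (1.978/1.96) ≈ 1.02 at 66.

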### Data Collection

After a couple gives informed consent, but before the couple is randomized to either the intervention or control group, each member of the couple is given a baseline survey. This survey is approximately 60-90 minutes long and collects data on demographics, relationship characteristics, sexual history, HIV care, and HIV prevention. In addition to survey data, biological samples are collected: STI testing, ART/preexposure prophylaxis (PrEP) drug adherence testing, and viral load testing. At the Boston site, however, STI testing is not conducted due to budgeting constraints.

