### Randomization

Upon individual completion of the check-in survey by both partners, couples are randomized to either the control arm (Individual Counseling) or the intervention arm (Couples Counseling). The treatment assignments are generated with the use of one pseudo-random number generator across all three study sites. The randomization process generates a random number between 0 and 100. If given an odd number, the couple is placed in the control treatment group; if given an even number, the couple is placed in the intervention treatment group.

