As secondary outcomes, the study measures sexual risk-taking and formation, and adherence of sexual agreements. For sexual agreements, participants are asked which of the following best describes their current sexual agreement with their main partner: (1) *both of us cannot have sex with outside partners*, (2) *we can have sex with outside partners, without any conditions or restrictions*, (3) *we can have sex with outside partners, but with some conditions or restrictions*, and (4) *we do not have an agreement*. Comparison of individual data will allow identification of discordant agreements. Participants will be asked if they have broken this agreement and whether this breakage was disclosed to their partner. To assess sexual behavior, measures adapted from the National HIV Behavioral Surveillance (NHBS) behavioral inventory collect information both on sexual behaviors with the main sex partner in the 3 months before the interview, and on sexual behaviors with all sex partners outside the relationship. For sex with the main partner, men are asked to estimate the number of anal sex acts with the main partner and the number of those acts that were condom-protected. For each partner outside the relationship, men are asked a series of questions to include characteristics of the outside partner, HIV status (if known), whether the sex outside the relationship was disclosed to the main partner, the number and type of sex acts, and the proportion of those sex acts that were protected by condoms. Additional outcomes assessed are centered on Couple’s Interdependence Theory.

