### Sample Size

Estimating 80% retention, we propose to enroll a sample of 165 male sero-discordant couples. The primary outcomes are engagement in HIV care and viral suppression. A sample of 165 sero-discordant couples provides statistical power (with 95% confidence and 80% power) to detect scientifically significant relative differences of 15%, 20%, and 25% in each of these outcomes between the two study arms. Additional health-enhancing behaviors include recent sexual risk-taking; using the data from our previous RCT of CHTC, this sample of 165 sero-discordant couples provides statistical power to identify significant differences in sexual risk-taking between the two arms. Using the methods described by Rosner for sample size estimation for longitudinal studies [67], a sample size of 75 couples in each group will ensure statistical power (using a two-sided two-sample t-test) to identify differences in the dyadic scale constructs between arms. As secondary outcomes, the study will examine sero-conversion and syphilis incidence between the two arms, although the power is insufficient to detect significance differences between the study arms.

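### The analysis of at-risk sex acts does not use the couple's own baseline count of condomless acts, which costs the arm IRR precision and leaves chance imbalance uncorrected

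*Protocol article*

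**What the plan says.** All references are to the protocol article.

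- **Outcome** (section on the incidence of aggregate sex at risk within partnerships): "At-risk sex will be defined as any CAI that occurs within the partnership during the follow-up period". Baseline acts are therefore not part of the outcome.
- **Model** (same section): period rates come from "performing a GEE Poisson regression analysis of the 6-monthly counts", "using an exchangeable correlation structure for the repeated observations of couples".
- **Covariates** (same section): "Baseline covariates include race, age, and duration of relationship". A later sentence says that results by each baseline covariate will be given as an IRR with its confidence interval.
- **Measurement** (Outcomes): for the 3 months before the interview, "men are asked to estimate the number of anal sex acts with the main partner and the number of those acts that were condom-protected". The difference between the two numbers is the condomless count.
- **Baseline data** (Data Collection): each partner completes a survey after consent and before randomization. "This survey is approximately 60-90 minutes long and collects data on demographics, relationship characteristics, sexual history, HIV care, and HIV prevention". Follow-Up Visits describes the later surveys as similar to this one.
- **Allocation** (Randomization): "The randomization process generates a random number between 0 and 100", with odd and even deciding the arm. One generator serves all three sites, and no stratification or blocking is described.
- **Power** (Sample Size): "this sample of 165 sero-discordant couples provides statistical power to identify significant differences in sexual risk-taking between the two arms".

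**The concern.** How often a couple had condomless sex before the trial is likely to predict how often it does so afterwards, and probably better than race or age. Act counts also vary widely between couples. If the model ignores the baseline level, that stable between-couple variation stays in the error of the arm comparison. If one arm happens to receive more couples with high baseline counts, part of that difference shows up in the estimated IRR.

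The design offers no protection, because allocation is simple and not stratified on sexual behaviour. Sexual risk-taking is a named secondary outcome for which the article claims adequate power, so precision lost at no saving bears on a stated aim. If nothing is prespecified, there is also room to choose between adjusted and unadjusted results once any baseline difference has been seen.

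**Working it through.** **1. The plan's own figure.** Sample Size gives 165 couples and 80% retention: 165 x 0.80 = 132 couples, or about 66 per arm. The power statement for sexual risk-taking cannot be reproduced, because no event rate, IRR, dispersion or power value is given for it.

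**2. Is the baseline count available?** Outcomes defines the items, Data Collection places a survey covering sexual history before randomization, and Follow-Up Visits says the later surveys resemble it. Together these indicate that the count is taken at baseline. This is an inference from three sections; no single sentence states it.

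**3. Gain in precision.** Let rho be the correlation, on the analysis scale, between a couple's baseline count and its follow-up level. Adjustment multiplies the variance of the log IRR by about 1 - rho^2, so the interval width is multiplied by sqrt(1 - rho^2). The equivalent number of couples is 132/(1 - rho^2). The article does not give rho, so the range is an assumption.

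| Assumed rho | 1 - rho^2 | CI on log IRR narrows by | Equivalent couples (from 132) |
|---|---|---|---|
| 0.2 | 0.96 | 2.0% | 138 |
| 0.3 | 0.91 | 4.6% | 145 |
| 0.5 | 0.75 | 13.4% | 176 |
| 0.7 | 0.51 | 28.6% | 259 |

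**4. Does the rule carry over to this model?** An exchangeable GEE Poisson model was simulated with 132 couples, four follow-up visits, a true IRR of 1, assumed log-normal variation between couples and visits, and 300 replicates per setting.

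| Correlation, baseline with follow-up | Adjusted/unadjusted SD of log IRR | sqrt(1 - rho^2) |
|---|---|---|
| 0.25 | 0.98 | 0.97 |
| 0.53 | 0.85 | 0.85 |
| 0.69 | 0.70 | 0.72 |
| 0.80 | 0.54 | 0.60 |

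The rule is a fair guide. Both estimators averaged about 0 on the log scale, so neither showed systematic bias.

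**5. Chance imbalance.** With 66 couples per arm, the standard error of a standardized baseline difference is sqrt(2/66) = 0.174. A gap of 0.3 SD is 0.3/0.174 = 1.7 standard errors, which is uncommon but plausible. Under a linear approximation, such a gap moves the unadjusted comparison by rho x 0.3/0.174 of its own standard error: 0.34 at rho = 0.2, 0.52 at 0.3, 0.86 at 0.5 and 1.21 at 0.7. In the four simulated settings the unadjusted log IRR correlated 0.24, 0.47, 0.58 and 0.66 with the baseline difference. After adjustment the correlations were between 0.00 and 0.12.

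**The case against.** **The sentence may not be an adjustment set.** The article goes on to summarise results by each baseline covariate and speaks of events per subgroup. Age, race and length of relationship return later as moderators. The verb *include* also need not be exhaustive. This stands: a reader might infer that the article fixes an adjustment set that excludes the baseline count, and the text does not establish that. The point survives because on neither reading is the baseline count used.

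**Nothing is biased.** This also stands. A reader might infer that the planned IRR is wrong or systematically distorted. Under randomization it is not. The cost is precision, and sensitivity to the imbalance in the particular sample drawn.

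**The gain is speculative.** Partly right. It rests on a correlation the article does not state, and near 0.2 it hardly matters. A reader might also turn the variance reduction into a rise from 80% power. The 80% in Sample Size belongs to the primary outcomes, so no such statement can be made for this outcome.

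**Retention is better than planned.** Results reports more than 90% at 24 months, so more than 66 couples per arm may be analysed. The percentage narrowing does not depend on the number of couples.

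**The covariate needs care.** Correct. Both partners report, so two counts must become one. Couples qualify after little more than a month together, so a 3-month recall can cover a truncated period. In addition, Check-In and Randomization tie allocation to the check-in survey, while Data Collection puts the baseline survey before randomization. The order should be confirmed. None of this is a reason to leave the variable out.

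**Conclusion.** The point holds as an inexpensive improvement to the analysis of a secondary outcome. The covariate sentence is ambiguous in purpose, but on either reading the arm IRR makes no use of a baseline measure that the trial appears to collect. The unadjusted IRR is valid on average. It gives up precision, and it carries any chance baseline difference, which the allocation method does nothing to limit.

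The size depends on the unstated correlation: about 2% to 5% off the interval width at 0.2 to 0.3, which is negligible to small, and 13% to 29% at 0.5 to 0.7, which is material. The conclusion assumes that the baseline survey contains the same act-count items as the follow-up surveys and is completed before allocation. The documents do not support calling the planned IRR biased, and they do not support a power figure for this outcome with or without adjustment.

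**What to change.** In the section on at-risk sex within partnerships:

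- State that the GEE Poisson model for the arm IRR includes log(baseline count of condomless anal acts with the main partner + 1), and say whether race, age and relationship duration are adjusters or factors for summarising results.
- Combine the two partners' baseline reports by the same rule used for the follow-up outcome.
- For couples together less than 3 months, express the count per month of exposure, then multiply by three before taking the log so that all couples are on one scale.
- Report the adjusted IRR as the main result and the IRR without this term as a sensitivity analysis.
- Confirm that the baseline survey precedes allocation.

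The 3-month baseline window need not match the 6-monthly follow-up periods, because the count enters as a covariate. The exact Poisson comparison planned for sparse subgroups can stay as it is.

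The cost is a few sentences and one model term, with no new data or visits. The small downside is that couples with a missing baseline count need a simple fill-in, for example the median taken without regard to arm plus a missing indicator.

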## Methods

### Design

The research activities involve a prospective RCT of approximately 165 venue- and clinic-recruited sero-discordant male couples (330 individuals: 165 HIV sero-negative and 165 HIV sero-positive). The study takes place in three cities: Atlanta, GA (study site Emory University); Boston, MA (study site The Fenway Institute); and Chicago, IL (study site Ann & Robert H. Lurie Children’s Hospital of Chicago). Cohort recruitment began in 2015. Couples are followed prospectively for 24 months, with study assessments at baseline, 6, 12, 18, and 24 months.

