### Participants

Eligible participants are cis-gender male couples in which: (1) two men report having been in a relationship with each other for greater than one month, with a relationship defined as, “having a male partner who you are committed to above all others”; (2) both men are aged over 18 years; (3) individuals have lived in the Atlanta, Boston, or Chicago metro areas for greater than 3 months; (4) participants reported no recent history (in the past 12 months) of IPV or coercion; and (5) an HIV sero-discordant relationship exists, in which both partners have disclosed their sero-status to each other. Prevalent HIV sero-positive statuses are self-reported and are not confirmed by study staff.

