### Follow-Up Visits

All couples in the prospective cohort return for follow-up visits at 6, 12, 18 and 24 months following the baseline survey visit. These visits consist of a survey similar to the baseline survey, biological sample collection, and either CTR for the HIV-negative partner in the control arm, information on adherence to ART for the HIV-positive partner in the control arm (but not counseling on adherence), or CHTC and Partner STEPS counseling for the intervention couples. CHTC is offered to control arm couples at the 24-month visit. At the 24-month visit, a sample of 30 couples (10 per city) is also invited to participate in a brief qualitative exit interview that inquires into evaluation of the study experience and perceived effectiveness of the counseling they received. Over the course of enrollment, couples also receive bi-monthly phone calls to check-in on their relationship and assess medication adherence. These phone calls also serve to help with retention.

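### At-risk sex is asked for the 3 months before each 6-monthly interview but analysed over all follow-up time, so absolute rates would be about half the true rate if the rate is constant

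*Protocol article*

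**What the plan says.** All references are to the protocol article.

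- **Schedule (Design):** "Couples are followed prospectively for 24 months, with study assessments at baseline, 6, 12, 18, and 24 months".
- **Recall (Outcomes):** the behavioural inventory covers "sexual behaviors with the main sex partner in the 3 months before the interview". Within that window, "men are asked to estimate the number of anal sex acts with the main partner and the number of those acts that were condom-protected". The count of condomless acts comes from the difference between these two numbers.
- **Follow-up instrument (Follow-Up Visits):** "These visits consist of a survey similar to the baseline survey, biological sample collection". No wider recall window is given. The bi-monthly calls are described for relationship check-in, medication adherence and retention, not for counting sex acts.
- **Analysis (Incidence of Aggregate Sex at Risk Within Partnerships):** at-risk sex is any condomless anal intercourse within the couple during follow-up. The incidence density has the number of such acts as numerator, "the denominator being person-years of follow time". The next sentence but one speaks of rates per couple-year. Period rates "of at-risk sex will be estimated by performing a GEE Poisson regression analysis of the 6-monthly counts". Arms are compared by the IRR.

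**The concern.** The article fixes the recall window, the visit spacing, the numerator, the denominator and the count period, and these do not fit together. A 3-month question asked every 6 months cannot give the number of acts in 6 months, nor a numerator for all follow-up time. Months 0–3, 6–9, 12–15 and 18–21 are never asked about.

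No other described source fills the gap. Later in the same section, information on STI testing, diagnosis and treatment received elsewhere is collected back to the previous study visit. So a full-interval window was stated where one was wanted, and sex acts were not given one.

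At stake is the absolute frequency of condomless acts in sero-discordant couples. A reader would take the published figure as acts per year, when its numerator covers only half the time in its denominator. The between-arm ratio is a separate question, taken up below.

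**Working it through.** The article states no expected rate, count or power figure for this outcome, so there is no figure of its own to reproduce. The check is direct arithmetic.

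**1. Coverage.** Inputs: 3 months of recall (Outcomes); follow-up interviews at 6, 12, 18 and 24 months (Design, Follow-Up Visits). The asked windows are months 3–6, 9–12, 15–18 and 21–24.
Coverage = 4 × 3 / 24 = 12/24 = 0.50.

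**2. Absolute rate, constant over time.** Assume for illustration 30 acts per couple-year, one report per act, in couple-years.
- Acts recorded in the asked 12 months: 30 × 1.0 = 30.
- Divided by all follow-up time: 30/2.0 = 15 per year, a ratio of 0.50.
- Divided by recall time: 30/1.0 = 30 per year, a ratio of 1.00.
- Per visit: 30 × 0.25 = 7.5 acts. Treated as a 6-month count, this gives 7.5/0.5 = 15 per year, again 0.50.

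**3. Absolute rate, not constant.** Let r be the rate in unasked months divided by the rate in asked months. Then reported/true = 1/(1 + r). The values of r are assumptions.

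| r | 0.5 | 0.75 | 1 | 1.5 | 2 |
|---|---|---|---|---|---|
| reported/true | 0.67 | 0.57 | 0.50 | 0.40 | 0.33 |

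**4. Counting unit.** The section uses both person-years and couple-years and does not say whose report of a shared act is counted. On the couple-year scale, at a constant rate, reported/true = 0.50 × (reports per act) / (denominator years per couple-year).

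| | couple-years | person-years |
|---|---|---|
| one partner's report | 0.50 | 0.25 |
| both partners' reports | 1.00 | 0.50 |

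The 1.00 is two errors cancelling, not a correct calculation.

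**5. IRR, effect over time.** The coverage factor is common to both arms and cancels if the effect is the same in asked and unasked months. With a constant control rate, IRR a in unasked and b in asked months, the true IRR is (a + b)/2 and the reported IRR is b.
- a = 0.8, b = 0.8: true 0.80, reported 0.80.
- a = 0.6, b = 0.8: true 0.70, reported 0.80.
- a = 0.8, b = 0.6: true 0.70, reported 0.60.

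A difference is possible by design. The adherence sessions at weeks 8 and 10, and the 3 months after each booster at 6, 12 and 18 months, all fall in unasked time.

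**6. IRR, missed interviews.** In a crude density where a missed interview keeps its time in the denominator and adds no acts, the null IRR equals the ratio of attendance. With an assumed 95% against 90%, it is 0.95/0.90 = 1.06. The Results section gives 95% average retention and over 90% at 24 months, but not by arm, so this shows direction only.

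**The case against.** The best defence is that this is an article. The phrase about 6-monthly counts may mean counts taken at 6-monthly visits, the follow-up survey is described as similar to the baseline survey rather than identical, and the offset of a Poisson model is the kind of detail left to a full plan. This limits how sure one can be that the rates will be halved in practice. It does not remove the stated denominator. A plan that used recall time would have to depart from the published text.

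Three stronger readings are tempting, and the document does not support them.

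- **The reported rate is certain to be half the true rate.** That requires a constant rate, no rescaling and one counting unit. The document establishes none of the three.
- **The comparison of arms is biased.** The common factor cancels in the IRR. Bias needs a different effect in unasked months, or unequal attendance combined with a crude density. No attendance difference by arm is reported, and the section does not say how time accrues after a missed visit. It also sends comparisons with at least 15 events per group to GEE; in a per-visit model a missed visit has no count and normally drops out.
- **The baseline window is too short for new couples.** Eligibility requires only that "two men report having been in a relationship with each other for greater than one month", so some couples have less than 3 months behind them at baseline. But the outcome counts acts during follow-up, so the baseline window does not enter the incidence. By the 6-month visit every intact couple has been together for more than 6 months.

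**Conclusion.** The mismatch between the recall window and the analysis is real and stands in the text. The incidence as defined cannot be computed from the data described. If 3-month counts are divided by full follow-up time, the absolute rate in both arms would be about 0.50 of the true rate, assuming a constant rate, no rescaling and one consistent counting unit. With unasked months at 2 to 0.5 times the asked rate, it would be about 0.33 to 0.67. The unsettled unit adds a further range of 0.25 to 1.00 on the couple-year scale at a constant rate.

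The IRR is largely preserved, with the two conditional exceptions shown in steps 5 and 6. Because the outcome is secondary and the main damage is to absolute rates, this is a should-fix.

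**What to change.** In the section on incidence of at-risk sex:

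1. Define the outcome as condomless acts with the main partner in the 3-month recall window at each follow-up interview, and replace the reference to 6-monthly counts accordingly.
2. Use as denominator or offset the recall time covered by each completed interview: 0.25 couple-years, or less if the couple separated within the window. A missed interview adds neither acts nor time.
3. Use couple-years throughout, and state in advance one rule for whose report of a shared act is counted. Without that rule, an offset of 0.25 couple-years would double the rate when both partners' reports enter.
4. Describe the result as a rate over the recall windows, not over the full 24 months.

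The cost is wording and an offset in the model; no new data are needed. The change corrects the absolute rate for the asked time. It cannot recover the unasked months, so the IRR will also describe the recall windows only, and the report should say so.
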